## Abstract

**Background:**

The majority of HBeAg-positive mothers with chronic hepatitis B have high levels of viremia and inactive disease with normal alanine aminotransferase (ALT) during pregnancy. In addition, postpartum disease activation and ALT flare have been reported in the range of 15 − 35%. However, the current International Association Guidelines have not provided clear recommendations and a risk-stratified monitoring schedule. Furthermore, data are lacking on the definition of normal ALT in the postpartum period in mothers with chronic hepatitis B. The clinical features and ALT flare patterns in HBeAg-positive mothers versus HBeAg-negative mothers are not fully explored. Thus, we design a cohort study to investigate the aforementioned area and generate data to assist healthcare providers in better managing mothers with hepatitis B. We aim to assess the frequency of postpartum ALT flares and predictors for such events.

**Method:**

This study is a single-center and prospective cohort study (n = 360) that consists of two groups of patients including HBsAg-positive mothers (n = 120) and healthy mothers without HBV infection (n = 240). In HBeAg-positive mothers, antiviral therapy during late pregnancy is permitted to prevent Mother-to-child transmission (MTCT) but discontinued at delivery if there is no further indication for the treatment. Mothers are enrolled at the gestational weeks of 12–24. After delivery, both mothers and their infants will be followed up until postpartum week 24. Clinical and laboratory data are collected every 4 weeks during the study except there are no follow-up visits at the postpartum weeks 16 and 20. The primary objective is the proportion of patients with postpartum ALT flares. The secondary objectives are independent risk factors during pregnancy for predicting postpartum ALT flares and the normal range of postpartum ALT levels in healthy mothers.

**Discussion:**

The current study focuses on the incidence of postpartum ALT flares in mothers with chronic hepatitis B including subgroup analysis based on HBeAg status. The data will have several clinical implications, such as providing evidence for an appropriate monitoring schedule in CHB mothers after delivery. Further analyses on predictors of such events may assist clinicians in identifying mothers who might develop severe postpartum ALT flares. The data generated from healthy mothers have the potential to identify the patterns of ALT changes during pregnancy and postpartum, so we can gain a better understanding of the normal range of ALT in this subpopulation.

**Trial Registration Number at the Chinese Clinical Trial Registry:**

ChiCTR2200061130.

## Background

Hepatitis B virus (HBV) infection is a serious threat to public health globally with a prevalence rate of up to 7% in Asia and Africa [1]. Chronic hepatitis B infection affects approximately 800 million individuals in China. Among them, approximately one million people die from cirrhosis or hepatitis B-associated liver cancer annually [1]. In the area with a high prevalence of hepatitis B, MTCT contributes largely to the new cases of HBV chronic infection [2]. The World Health Organization (WHO) has set a goal to eliminate HBV infection by 2030. Thus, the prevention of MTCT and the management of mothers with hepatitis B are critical steps to achieve the goal set by the WHO. It is estimated that the prevalence rate of hepatitis B infection in childbearing-age women in China is 6.61% [3]. Current practice guidelines [4–6] recommend that mothers with HBV DNA levels over 200,000 IU/mL should receive antiviral treatment during pregnancy to reduce the risk of MTCT. However, detailed guidance is lacking on the postpartum management of mothers with chronic hepatitis B. The practice patterns are inconsistent across different clinical settings in terms of when to stop the antiviral therapy and how to monitor mothers after delivery due to lacking high-quality evidence.

In young mothers with hepatitis B infection and high viral load without significant hepatitis, postpartum disease activation or hepatitis flare has been reported in the range of 15-35% [7, 8]. In a multicenter and prospective randomized controlled trial (RCT), Pan et al. observed that postpartum ALT elevation occurs in both mothers who were treated with tenofovir disoproxil fumarate (TDF) or received no therapy during pregnancy (45% vs. 30%) [9]. Another prospective study also showed that 36.3% of pregnant women who received antiviral therapy during pregnancy had postpartum hepatitis flares. Some of the ALT flares might further progress to acute exacerbation of hepatitis or even hepatic decompensation without timely antiviral treatment [7, 8]. In mothers without antiviral treatment during pregnancy, a large retrospective cohort study with 4236 hepatitis B mothers in China found that the postpartum ALT elevation rate was 28.27% [9]. Several independent predictors for postpartum ALT elevations were found in this subpopulation, which included high viral load or elevated transaminase during pregnancy. The peak period of ALT flares occurred between postpartum weeks 4–6 and weeks 9–12, with a bimodal distribution [9]. However, the study noted several limitations, including the lack of data on maternal virological features such as genotype, basal core promoter, pre-core mutation, and pre-S mutant. In addition, the postpartum follow-ups were within 12 weeks in most mothers. In chronic hepatitis B patients at the immune tolerance phase, basal Core Promoters (BCP) and pre-core (PC) mutations are common in HBeAg-positive patients (up to 60%) and have been linked to immune activation [10, 11]. Recently, a study by Luo et al. [12] suggests that the mutations of PC and BCP in HBeAg-positive pregnant women during antepartum could predict spontaneous HBeAg seroconversion after delivery. However, the postpartum elevation of ALT or hepatitis B flares has not been clearly described and analyzed.

Because of the inconsistent data and the lack of details, the current International Association Guidelines have not provided clear recommendations and a risk-stratified monitoring schedule. Furthermore, data are lacking on the definition of normal ALT in the postpartum period in mothers with chronic hepatitis B. Lastly, the clinical features and ALT flare patterns have not been well defined in HBeAg-positive mothers versus HBeAg-negative mothers. Furthermore, fewer data are available to address differences regarding the normal range of ALT between pregnant mothers and the general population. In a cross-sectional study by Kushner T et al. [13], the prevalence of elevated ALT in pregnancy was assessed. The authors suggested that abnormal ALT in pregnant mothers should be defined as ALT ≥ 25 U/L. However, Lee SM et al. [14] proposed a different normal range of ALT by assessing the 95 percentile ALT value in mothers in the first trimester. The authors defined the upper limit of normal as 30 U/L. The study also showed that elevated ALT to levels above 30 U/L in early pregnancy was associated with the risk of subsequent development of gestational diabetes and preeclampsia in late pregnancy. Because of the controversy on the definition of normal ALT, we believe that our study on ALT levels in healthy mothers not only helps to clarify the appropriate reference range for ALT but also takes an important step to further define ALT flares in mothers with CHB. We hypothesize that the frequency and severity of postpartum ALT flares differ between chronic hepatitis B mothers and healthy mothers. Furthermore, the patterns of postpartum ALT flares may also be influenced by the HBeAg status or antiviral therapy during pregnancy. Therefore, we will conduct a prospective cohort study and assess the incidence of postpartum ALT flares in mothers with chronic hepatitis B with subgroup analysis based on HBeAg status. In addition, we evaluate the normal range of postpartum ALT in healthy mothers without hepatitis B. In mothers with hepatitis B, the independent risk factors for predicting postpartum ALT flares are also investigated. Our data will serve as a piece of evidence to assist healthcare providers in the better management of mothers with hepatitis B.

## Methods

### Research setting

This single-center cohort study will enroll mothers with chronic hepatitis B and healthy mothers in a university medical center in China. Patients are eligible for the study after the screening with the following inclusion and exclusion criteria:

#### Inclusion criteria

HBsAg (+) group: pregnant women aged 20–35 who are HBsAg-positive for more than 6 months, singleton pregnancy, gestational age between 12 and 24 weeks, HBV DNA > 2000 IU/mL, ALT normal for 2 consecutive times (at least ≥ 30 days apart), Liver stiffness measurement (LSM) < 7.4Kpa and controlled attenuation parameters (CAP) < 259 dB/m;Healthy pregnant women group: During the same period, pregnant women aged 20–35 with negative HBsAg and HBcAb who are treated in the Fifth Affiliated Hospital of Guangzhou Medical University, singleton pregnancy, and have two consecutive normal ALT (at least 30 days apart), LSM < 7.4Kpa and CAP < 259 dB/m. (Basically matched with the pregnant mothers in the HBsAg (+) group in terms of age, body Mass Index (BMI), and parity)

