#### Exclusion criteria

Co-infection of the human immunodeficiency virus (HIV), hepatitis D virus (HDV), hepatitis C virus (HCV), syphilis;Previous pregnancies with a history of miscarriage or congenital malformation;Treatment experience (unless antiviral drugs had been used in previous pregnancies to prevent MTCT and were discontinued more than 6 months before the current pregnancy);History of renal insufficiency; evidence of liver cancer or decompensation, estimated creatinine clearance rate (CLCr) < 80ml/L;Clinical symptoms of threatened abortion; ultrasonic evidence of fetal malformation;Co-committed use of nephrotoxic drugs, steroids, cytotoxic drugs, non-steroidal anti-inflammatory drugs, or immunomodulators; recipients of solid organ or bone marrow transplants; or diseases including severe renal, cardiovascular, pulmonary, or nervous system at the discretion of researchers;Fetal biological father is infected with chronic hepatitis B;ALT increased during this pregnancy before admission;Thyroid dysfunction;Chronic liver disease except for hepatitis B;Previous pregnancy complications, such as intrahepatic cholestasis of pregnancy (ICP), gestational hypertension, gestational diabetes, and proteinuria in pregnancy.

Subjects meeting any exclusion criteria will be excluded from participating in this study. Written informed consent must be obtained from all participating pregnant women before any screening activities are initiated.

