### Study endpoints

The primary endpoints are the proportion of HBsAg (+) pregnant women with elevated ALT within 24 weeks postpartum and the frequency of persistently elevated ALT for more than 12 weeks in HBsAg (+) pregnant women. Secondary endpoints include the proportion, peak, and period of ALT elevation in healthy pregnant women within 24 weeks postpartum; and the comparison of the secondary endpoints between the HBsAg (+) pregnant women group and healthy pregnant women group.

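### The postpartum ALT normal range is to come from healthy mothers already selected for normal antenatal ALT, which biases the limit low; the postpartum endpoint can also count elevations that began before delivery

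*Protocol article*

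**What the plan says.** **Entry.** The Inclusion criteria require that healthy mothers "have two consecutive normal ALT (at least 30 days apart". The HBsAg (+) group has the same kind of condition: "ALT normal for 2 consecutive times (at least ≥ 30 days apart". The Exclusion criteria, which apply to all subjects, add "ALT increased during this pregnancy before admission". The article gives no figure for normal at entry. Its Background calls the definition of normal ALT controversial and cites two candidate limits for pregnancy, 25 and 30 U/L.

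**Use of the healthy group.** The Abstract (Method) lists as a secondary objective "the normal range of postpartum ALT levels in healthy mothers". The Background says that the healthy-mother data "helps to clarify the appropriate reference range for ALT but also takes an important step to further define ALT flares in mothers with CHB".

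**Primary outcome.** The Abstract states: "The primary objective is the proportion of patients with postpartum ALT flares". Study endpoints states: "The primary endpoints are the proportion of HBsAg (+) pregnant women with elevated ALT within 24 weeks postpartum", with a second primary endpoint of elevation lasting more than 12 weeks. The 26% in the sample-size paragraph (Recruitment) rests on published rates of ALT elevation.

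**Blood sampling.** Table 1 schedules blood tests at entry, at weeks 28, 32 and 36, at delivery, and at postpartum weeks 4–8, 12 and 24.

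**The concern.** A reference limit should come from people chosen because they are healthy, not because the measurement in question was already low. Screening on HBsAg, HBcAb, liver stiffness and CAP is ordinary selection on health. Requiring two normal ALTs and no earlier rise is selection on the analyte. Women whose ALT habitually runs high, though they are well, are removed before the limit is estimated. An analysis plan cannot undo this, because the women are never enrolled. A limit presented as the general postpartum normal range would label too many healthy women abnormal. The article offers that limit as a step towards defining flares, so the error would travel with it.

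The second matter is timing. Entry closes by gestational week 24, and nothing in the endpoint requires ALT to be normal at delivery. An elevation that begins between entry and delivery and is still present afterwards counts as postpartum, although the article aims at disease activation after delivery.

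The third is wording. The objective speaks of flares, while the endpoints and the sample size speak of elevation. A reported proportion with flares could then mean ALT just above the limit.

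**Working it through.** **1. Direction of the bias.** Selection acts on two antenatal values; the limit is taken from postpartum values. With zero within-woman correlation, selection leaves the postpartum distribution unchanged. With any positive correlation, women with high postpartum ALT are under-represented and the upper percentiles fall.

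**2. Size, on assumed inputs.** The plan states no reference limit or ALT distribution, so there is no figure of its own to reproduce. None of the distributional inputs below is in the documents. Of the entry limits, 25 and 30 U/L are the values cited in the Background; 40 U/L is an assumed laxer limit.

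- Model: ln(ALT) at occasion j = ln 15 + 0.5·(√ρ·u + √(1−ρ)·e_j), with u and e_j independent standard normal and ρ the within-woman correlation.
- Unselected postpartum percentiles: 95th = 15·exp(0.5 × 1.645) = 34.1 U/L; 97.5th = 15·exp(0.5 × 1.960) = 40.0 U/L.
- Entry: both antenatal values below U. With c = ln(U/15)/0.5, the chance of passing given u is Φ((c − √ρ·u)/√(1−ρ))². Here c = 1.02, 1.39 and 1.96 for U = 25, 30 and 40.
- Distribution among women who pass: F(y) = ∫Φ((y − √ρ·u)/√(1−ρ))·P(pass|u)·φ(u)du ÷ ∫P(pass|u)·φ(u)du, where y = ln(postpartum ALT/15)/0.5. Solve F(y) = 0.95 and 0.975 numerically.

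Results for ρ from 0.4 to 0.6:

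| Entry limit (U/L) | 95th percentile, selected | Shortfall from 34.1 | 97.5th percentile, selected | Shortfall from 40.0 | Unselected healthy women above the selected 97.5th |
|---|---|---|---|---|---|
| 40 | 32.8 to 31.9 | 4 to 7% | 38.2 to 36.8 | 4 to 8% | 3.1 to 3.6% |
| 30 | 31.2 to 29.3 | 9 to 14% | 36.2 to 33.6 | 10 to 16% | 3.9 to 5.3% |
| 25 | 29.7 to 27.3 | 13 to 20% | 34.4 to 31.2 | 14 to 22% | 4.8 to 7.2% |

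The last column should be 2.5% for an unbiased limit.

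**3. Sensitivity.** A wider grid (median 14 to 16 U/L, log-SD 0.45 to 0.50, antenatal–postpartum correlation 0.3 to 0.7, the two screening values correlated at 0.6 or more, entry limits 25, 30 and 40 U/L) puts the 97.5th percentile 1 to 29% low. The entry limit and the correlation drive the size.

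**4. Carry-over.** ALT is checked as normal up to entry, at week 24 at the latest. The endpoint window runs from delivery to postpartum week 24. Between the two, the endpoint sets no condition on ALT, so an elevation first seen at week 28, 32, 36 or delivery and persisting after birth meets the endpoint wording. Table 1 already collects those samples, so such women can be identified.

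**5. Terms.** The Abstract objective says flares; Study endpoints and the sample-size paragraph say elevation. The same 45% versus 30% result is called ALT elevation in the Background and ALT flares in the Discussion. Statistical methods seeks predictors of flares, then a ROC curve for ALT rise. The words are used interchangeably.

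**The case against.** The strongest reply is that the bias may be small. With a 40 U/L entry limit the 97.5th percentile falls only from 40.0 to about 37–38 U/L. With the planned 216 completers, the sampling 95% interval of an empirical 97.5th percentile is about 33.5 to 46.7 U/L under the same assumptions. That stands as a limit on size. It does not remove the bias, which is systematic and grows with a stricter entry limit.

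A reader might also infer stronger claims that the documents do not support:

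- *The upper tail is cut off.* It is not. Selection is on pregnancy values, so the postpartum tail is thinned and values above the entry limit remain possible.
- *The group comparison is biased.* Both groups carry the same two-normal-ALT condition and the same exclusion, so this criterion does not by itself unbalance them.
- *The healthy group's elevation rate is fixed by construction because these women will be scored against their own percentile.* Nothing says so. The choice of threshold may properly sit in the full protocol or analysis plan.
- *Flare and elevation are two different outcomes and the wrong one was powered.* The article treats them as synonyms, and it separately plans a mild/severe split and a persistence endpoint. What remains is inconsistent wording.

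Finally, separating new from carried-over elevations could be left to an analysis plan. That is fair, but the endpoint as worded admits both, and the planned data allow the split.

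**Conclusion.** The point holds in a limited form. Following the plan as written gives a postpartum ALT limit that is too low for healthy mothers in general, provided that ALT is positively correlated within women. The size cannot be derived from the documents. Under the stated assumptions the shortfall at the 97.5th percentile is 4 to 8% with an entry limit of 40 U/L, 10 to 16% with 30 U/L and 14 to 22% with 25 U/L. The limit is valid for what the sample is: women with two normal antenatal ALTs and no earlier rise in this pregnancy.

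The primary endpoint can also count elevations that began before delivery; how many cannot be estimated from the article. The flare/elevation mismatch is real but editorial.

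**What to change.** (a) Present the derived limit as the postpartum ALT limit in women with two normal antenatal ALTs, alongside the laboratory limit applied at entry, and drop the claim to a general normal range. Where screening records allow, report how many otherwise eligible healthy candidates were turned away on ALT alone. Recruitment has begun, so the entry rule itself cannot simply be reset, and the article does not show whether such a log exists.

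(b) Report new postpartum elevations (ALT normal at the last antenatal or delivery sample) separately from carried-over ones, in both groups, using the week 28–36 and delivery blood tests already in Table 1.

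(c) Use ALT elevation in the primary objective, to match the endpoints and the sample-size basis.

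Cost: a narrower normal-range claim, a count from the screening records if they exist, and a little more analysis. No new visits or samples are needed.

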#### Exclusion criteria

Co-infection of the human immunodeficiency virus (HIV), hepatitis D virus (HDV), hepatitis C virus (HCV), syphilis;Previous pregnancies with a history of miscarriage or congenital malformation;Treatment experience (unless antiviral drugs had been used in previous pregnancies to prevent MTCT and were discontinued more than 6 months before the current pregnancy);History of renal insufficiency; evidence of liver cancer or decompensation, estimated creatinine clearance rate (CLCr) < 80ml/L;Clinical symptoms of threatened abortion; ultrasonic evidence of fetal malformation;Co-committed use of nephrotoxic drugs, steroids, cytotoxic drugs, non-steroidal anti-inflammatory drugs, or immunomodulators; recipients of solid organ or bone marrow transplants; or diseases including severe renal, cardiovascular, pulmonary, or nervous system at the discretion of researchers;Fetal biological father is infected with chronic hepatitis B;ALT increased during this pregnancy before admission;Thyroid dysfunction;Chronic liver disease except for hepatitis B;Previous pregnancy complications, such as intrahepatic cholestasis of pregnancy (ICP), gestational hypertension, gestational diabetes, and proteinuria in pregnancy.

Subjects meeting any exclusion criteria will be excluded from participating in this study. Written informed consent must be obtained from all participating pregnant women before any screening activities are initiated.

### Research scheme

This study will be a single-center, prospective, open-label cohort study, from 12 to 24 weeks of pregnancy to postpartum week 24. Eligible pregnant women who are registered in the Fifth Affiliated Hospital of Guangzhou Medical University for delivery are enrolled at the 20–24 weeks of gestation and assigned into the HBsAg (+) group and healthy pregnant women group based on their HBsAg status. Patients are monitored every 4 weeks until delivery and then every 6, 12, and 24 weeks postpartum (Fig. 1). The recruitment of patients for this study began on June 1, 2022, and is expected to be completed on June 1, 2023.

**Fig. 1 Fig1:**
[figure not shown]
Patient Enrollment and Assessment

### Recruitment

Subjects will be recruited through the Department of Infectious Diseases and Obstetrics Clinic of the Fifth Affiliated Hospital of Guangzhou Medical University. Recruitment began in June 2022. Based on the published literature [7, 9, 15] the frequency of elevation ALT in HBV-infected pregnant women during the postpartum period is estimated at the range of 11.6–30.6%. We calculate the sample size for the current study (presume p = 26%, q = 10%, type I error α = 0.05, test efficiency 1-β = 0.9) in the HBsAg (+) group and set the number of patients to approximately 120. In the healthy mother group, 240 subjects are planned to be enrolled (HBV mothers: healthy mothers at the 1:2 ratio). The total of subjects in the study will be 360. We estimate about 5-10% of subjects may withdraw from the study. The total number of patients who have completed data at the end of the study will be 108 in the HBsAg (+) group and 216 in the healthy pregnant women group, respectively. The sample size will provide enough to observe the adverse events with an incidence of 3% or greater.

### Trial intervention

Although our study is observational, due to the compliance with the practice guidelines recommended by the national professional association, mothers with high levels of HBV viremia will receive antiviral treatment during pregnancy and all infants will receive HBIG and HBV vaccines. These medical products are independently prescribed for participants in the study and are part of a standard care treatment strategy, which is not determined in advance by our research protocol. These treatments are applied based on clinical practice. However, we will assess the safety of mothers and newborns who receive the intervention. There will not be trial-specific intervention implemented in the study.

